**5.4.4.1.3. Cohort A data review by the SMC prior to vaccinations in Cohort B and Cohort C:**

An interim unblinded SMC report including all available safety and reactogenicity data, will be produced by an independent statistician according to an agreed pre-defined Report and Analysis Plan, after the Cohort A has completed the one month post challenge visit. The SMC will review this report prior to authorizing vaccinations to proceed in Cohort B and Cohort C. Vaccination of the next cohort of study participants can be put on hold by the SMC if either of the following sets of holding criteria described below is met:

*Holding rules*

- Solicited local adverse events:
  - More than 25% of Ad35.CS.01 doses are followed by Grade 3 solicited local adverse event beginning within 2 days after Ad35.CS.01 vaccination (day of vaccination and one subsequent day) and persisting at Grade 3 for > 2 consecutive days
  - More than 25% of first doses of RTS,S/AS01B in subjects having received Ad35.CS.01 are followed by Grade 3 solicited local adverse event beginning within 2 days after vaccination (day of vaccination and one subsequent day) and persisting at Grade 3 for > 2 consecutive days
  - More than 25% of second doses of RTS,S/AS01B in subjects having received Ad35.CS.01 are followed by Grade 3 solicited local adverse event beginning within 2 days after vaccination (day of vaccination and one subsequent day) and persisting at Grade 3 for > 2 consecutive days
- Solicited systemic adverse events:
  - More than 25% of Ad35.CS doses are followed by Grade 3 solicited systemic adverse event estimated to be related to vaccination beginning within 2 days

after Ad35.CS.01 vaccination (day of vaccination and one subsequent day) and persisting at Grade 3 for > 2 consecutive days

- More than 25% of first doses of RTS,S/AS01B in subjects having received Ad35.CS.01 are followed by Grade 3 solicited systemic adverse event estimated to be related to vaccination beginning within 2 days after vaccination (day of vaccination and one subsequent day) and persisting at Grade 3 for > 2 consecutive days
- More than 25% of second doses of RTS,S/AS01B in subjects having received Ad35.CS.01 are followed by Grade 3 solicited systemic adverse event estimated to be related to vaccination beginning within 2 days after vaccination (day of vaccination and one subsequent day) and persisting at Grade 3 for > 2 consecutive days
- Unsolicited adverse events
  - a serious adverse event considered related to vaccination occurs in a study participant from the Ad35.CS.01 – RTS,S/AS01B – RTS,S/AS01B group
  - more than 25% of subjects from the Ad35.CS.01 – RTS,S/AS01B – RTS,S/AS01B group develop any Grade 3 unsolicited adverse event considered related to vaccination and persisting at Grade 3 for > 2 consecutive days.
- Standard neurological evaluation
  - more than 10% of subjects from the Ad35.CS.01 – RTS,S/AS01B – RTS,S/AS01B group develop abnormal neurological symptoms captured by standardized neurological evaluation ([Appendix B](#)).
- Laboratory adverse events
  - more than 25% of subjects from the Ad35.CS.01 – RTS,S/AS01B – RTS,S/AS01B group develop any Grade 3 laboratory adverse event considered related to vaccination.
  - more than 10% of subjects develop hematuria, not taking into account menstruating females if the hematuria coincides with their regular monthly time for their period or urinary tract infection.

If a holding rule has been met, vaccination of subjects in the subsequent cohort will only start if GSK, Crucell, MVI and investigators agree to it, following discussions with the SMC. All IRBs will be notified if a holding rule is activated or released after SMC review.

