#### **5.4.3. Malaria Challenge**

Volunteers from both study groups completing their immunization course will be challenged with sporozoite-infected mosquitoes to determine whether the expected protective response has developed. Such challenges are mandated by the absence of any laboratory tests that will unequivocally predict protection. The challenge is scheduled to occur approximately 21 days (3 weeks) after the last vaccination visit (Study Day 77) and will be performed in a staggered fashion. The first 56 eligible subjects (28 subjects per study group) will be enrolled and vaccinated (Cohort A). Among the 56 vaccinated individuals a random selection of subjects eligible for challenge will be done according to the local SOP to ensure that a maximum of 46 vaccinated individuals (balanced by group) will progress to the challenge phase. The remaining subjects will not be challenged but will be followed for safety and immunogenicity up to 6 months after the last vaccination.

Unimmunized infectivity control volunteers will also be challenged to verify the adequacy of the challenge. The use of 4 to 6 unimmunized, malaria-naïve controls per challenge day is adequate since the procedure described has generally successfully infected such volunteers [Gordon, 1995]. The challenge of vaccinated subjects from Cohort A will be done at the WRAIR Insectary.

After safety and efficacy assessment for Cohort A, subjects from Cohort B and C (approximately 56 subjects per cohort) will be vaccinated. Of these subjects, a maximum of 46 vaccinated study participants per cohort will progress to the challenge phase. The challenge of Cohorts B and C will be conducted in parallel at WRAIR Insectary and the University of Maryland, CVD, respectively. Malaria-infected mosquitoes for challenge at the University of Maryland will be transported by WRAIR investigators to the insectaries at the University of Maryland for challenge of human subjects.

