**Table 7 List of study procedures – Screening epoch (vaccinees and infectivity controls)**

| Epoch                                                                                                       | Screening epoch |                |
|-------------------------------------------------------------------------------------------------------------|-----------------|----------------|
| Study visit                                                                                                 | 1               | 2 † |
| Study day                                                                                                   | -90 to -3       | -7 to -1       |
| Screening, briefing, informed consent                                                                       | ●               |                |
| Comprehension assessment                                                                                    | ○               |                |
| Check inclusion/exclusion criteria                                                                          | ●               | ●              |
| Assign subject number                                                                                | ●               |                |
| Record demographic data                                                                                     | ●               |                |
| Medical history                                                                                             | ●               |                |
| Physical examination                                                                                        | ●               | ○              |
| Check NHANES I criteria and EKG                                                                             | ●               |                |
| Pregnancy test: urine $\beta$ -HCG                                                                          | ●               |                |
| Reporting of SAEs related to study participation or to a concurrent GSK medication/vaccine or any fatal SAE | ●               | ●              |
| Record any concomitant medication/vaccination                                                               | ●               | ●              |
| Urine analysis for safety **                                                                                | ●               |                |

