|                           | 60       | ml   | Visit 14 (D42)                                                                                                                                                 | 168               |
|                           | 101      | ml   | Visit 20 (D77)                                                                                                                                                 | 168 (+12 to 18§)  |
|                           | 16       | ml   | Visit 22 (D82)                                                                                                                                                 | 168 (+12 to 18§)  |
|                           | 2        | ml   | Visit 23 (D83), Visit 24 (D84), Visit 25 (D85), Visit 26 (D86), Visit 27 (D87), Visit 28 (D88), Visit 29 (D89), Visit 30 (D90), Visit 31 (D91), Visit 32 (D92) | 168 (+12 to 18§)  |
|                           | 9        | ml   | Day of parasitemia (undetermined)                                                                                                                              | Undetermined      |
|                           | 2        | ml   | Visit 34 (D94), Visit 35 (D95), Visit 36 (D97), Visit 37 (D99), Visit 38 (D101), Visit 39 (D103)                                                               | 168 (+12 to 18§)¶ |
|                           | 91       | ml   | Visit 40 (D105)                                                                                                                                                | 168 (+12 to 18§)  |
|                           | 87       | ml   | Visit 41 (D140)                                                                                                                                                | 168 (+12 to 18§)  |
|                           | 87       | ml   | Visit 42 (D236)                                                                                                                                                | 168 (+12 to 18§)  |
| Urine (safety assessment) | -        | -    | Screening Visit 1 (D-90 to -3), Visit 6 (D6), Visit 9 (D28)                                                                                                    | 168               |

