### Hematological, biochemical and urine assays

Hematological testing (WBC, haemoglobin, and platelets), biochemical testing (ALT, AST and creatinine) and urinalysis (protein, blood) will be measured at regular intervals throughout the study period as listed in [Table 6](#).

Hematological, biochemical and urine testing will be performed at Quest or LabCorp laboratories using laboratory SOPs.

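### The Cohort A hematuria holding rule is the only one of eleven not tied to Ad35.CS.01 recipients; read literally, it is met at 6 of 56 rather than 3 of 28

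*Protocol*

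**What the plan says.** Protocol section 5.4.4.1.3 has the Safety Monitoring Committee (SMC) review Cohort A before Cohorts B and C are vaccinated, using "An interim unblinded SMC report including all available safety and reactogenicity data". Section 5.4.3 fixes the size of Cohort A: "28 subjects per study group) will be enrolled and vaccinated (Cohort A"), so 56 in all. Elsewhere the cohort size is given as approximate.

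The holding rules number eleven: three on solicited local events, three on solicited systemic events, two on unsolicited events, one neurological and two laboratory. The last two bear on this point:

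- **Laboratory, first bullet:** more than 25% of subjects from the Ad35.CS.01 – RTS,S/AS01B – RTS,S/AS01B (ARR) "group develop any Grade 3 laboratory adverse event considered related to vaccination".
- **Laboratory, second bullet:** "more than 10% of subjects develop hematuria, not taking into account menstruating females" when the bleeding falls at their regular period; urinary tract infection is also excepted.

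The neurological rule, the only other one with a 10% threshold, begins "more than 10% of subjects from the Ad35.CS.01" and goes on to name the full ARR regimen.

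When a rule is met, the next cohort starts only if the sponsor, its partners and the investigators agree after discussion with the SMC. All IRBs are told when a rule is activated or released.

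Section 1.1.2 explains why hematuria is watched. In the earlier Ad35.CS.01 study, positive urine blood tests were more frequent in the vaccine groups than under placebo, and all affected subjects were menstruating women.

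**The concern.** The other ten rules look only at people who received Ad35.CS.01. The hematuria rule alone says just subjects, with no group. Its literal denominator is therefore all Cohort A vaccinees, half of whom never received the product that prompted the check. Pooling doubles the number of cases needed, so with none in RRR the ARR group must reach twice the nominal 10% before the criterion is met. It also lets RRR cases alone meet the criterion, because this rule has no relatedness condition.

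Blinding gives no reason to pool, since the report under review is unblinded. Nothing else in the protocol settles the denominator: the individual stopping rule on hematuria in the same section concerns withdrawal of a single person.

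What is at stake is whether a pre-set safety criterion counts as met, and so whether the steps of agreement between the parties and notice to the IRBs are set in motion.

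**Working it through.** The protocol gives no case count for this rule, so there is no stated figure to reproduce.

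**Rules by group.** 3 local + 3 systemic + 2 unsolicited + 1 neurological + 2 laboratory = 11. Ten name Ad35.CS.01 doses, RTS,S/AS01B doses in Ad35.CS.01 recipients, or the ARR group. One, hematuria, does not.

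**Trigger counts.** The rule is met at the smallest whole number k with k/n > 0.10.

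- ARR reading, n = 28: 0.10 × 28 = 2.8, so k = 3 (3/28 = 10.7%).
- Literal reading, n = 56: 0.10 × 56 = 5.6, so k = 6 (6/56 = 10.7%). With no RRR cases this means 6/28 = 21.4% of ARR.

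The trigger stays at 3 for any n from 20 to 29 and at 6 for any n from 50 to 59. A slightly different cohort size therefore does not remove the difference.

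**Where the readings part.**

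| ARR cases | RRR cases | ARR reading | Literal reading |
|---|---|---|---|
| 3 | 0 to 2 | met (10.7%) | not met (3 to 5 of 56; 5.4% to 8.9%) |
| 4 | 0 or 1 | met (14.3%) | not met (4 or 5 of 56; 7.1% or 8.9%) |
| 5 | 0 | met (17.9%) | not met (5 of 56; 8.9%) |
| 2 | 4 or more | not met (7.1%) | met (6 or more of 56) |
| 1 | 5 or more | not met (3.6%) | met |
| 0 | 6 or more | not met | met |

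**Cost of the lower trigger.** Tables 7 and 8 schedule two urine tests after baseline, at Day 6 and Day 28. Suppose a background chance p of a countable positive per sample, the same in both arms, with independent samples. The chance per subject is q = 1 − (1 − p)². The protocol gives no p, so the values below are assumptions.

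| p | q | P(at least 3 of 28) | P(at least 6 of 56) |
|---|---|---|---|
| 1% | 0.0199 | 0.018 | 0.001 |
| 2% | 0.0396 | 0.098 | 0.023 |

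**How often the readings would disagree.** This depends on an ARR rate that the protocol does not give. With no RRR cases, P(3 to 5 cases in 28) is 0.018, 0.050 and 0.16 at assumed ARR rates of 2%, 3% and 5%. At assumed rates of 10% and 20% it is 0.49 and 0.44, falling to about 0.36 and 0.26 if RRR carries the 2% background per sample used above.

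**The case against.** The text does not contradict itself. Subject has a plain meaning, and the glossary extends it to both product recipients and controls. The hematuria rule also drops the Grade 3 and relatedness conditions of the bullet above it, so a broader rule may have been meant. The SMC works under a charter, and its report follows a pre-defined analysis plan. Neither is at hand, and either could fix the denominator. All of that stands as a reason to let the sponsor say which reading is intended. It does not answer the main point: the criterion is written in the protocol, and taken at its word it dilutes a check prompted by Ad35.CS.01 recipients with an equal number of people who never received it.

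A reader might infer that the missing phrase decides whether Cohorts B and C are vaccinated. The documents do not support that. The SMC may hold but need not, and it must review the unblinded report before authorizing further vaccination whether or not a rule is met. Between doses it sees laboratory data tabulated by group, and the principal investigator may ask for a hold on any event. Three to five ARR cases against none in RRR would be noticed.

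A reader might also take the disagreement chances of nearly one half as the expected size of the problem. They rest on ARR rates of 10% to 20% that have no source, and on no RRR cases. The earlier hematuria cases were all in menstruating women, whom the rule largely excludes.

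Appendix C says that "urinalysis (protein, blood) will be measured at regular intervals throughout the study period as listed in" Table 6, which might suggest that urine is tested after doses 2 and 3. Table 6 is a blood-sampling table with no urine row. The operative rows, headed "Urine analysis for safety", are in Tables 7 and 8: screening, Day 6 and Day 28. Table 13 gives the same days but prints "Screening Visit 1 (D-90 to -3), Visit 6 (D6), Visit 9 (D28"), although Day 6 is Visit 7. These slips are clerical and do not change the threshold.

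**Conclusion.** The point holds as a missing group in one safety criterion. Read literally, the hematuria rule is met at 6 of about 56 pooled vaccinees; written like the other ten rules, it would be met at 3 of 28 in ARR. ARR counts of 3 to 5 with a two-arm total of 5 or fewer meet only the ARR version, and 0 to 2 ARR cases with a total of 6 or more meet only the literal one. These counts rest on the planned sizes alone and are stable to small changes in them.

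The practical stakes are limited. The wording governs whether the criterion is formally met, with the agreement and notification that follow, and not whether the SMC can see or act on an imbalance. How often the two readings would differ in practice cannot be stated from the protocol, because it gives no hematuria rate for either group. The change is still worth making, because it corrects a pre-set safety threshold at almost no cost in the first trial to combine these vaccines in one schedule.

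**What to change.** In section 5.4.4.1.3, start the hematuria rule as the neurological rule starts, "more than 10% of subjects from the Ad35.CS.01" – RTS,S/AS01B – RTS,S/AS01B group, and add the count: at least 3 of 28. Keep the exclusion for menses and urinary infection. Show the RRR count beside it in the SMC report. If pooling is intended, say so and give that count: at least 6 of 56.

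The cost is one phrase and no new procedure. The lower trigger raises the chance of a false hold, from 0.023 to 0.098 at the assumed 2% background and from 0.001 to 0.018 at 1%. The existing exclusion and release after SMC review limit the harm.

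As housekeeping only, refer Appendix C to Tables 7 and 8 for urine, and correct the Day 6 visit in Table 13 to Visit 7.

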### *Individual stopping rules*

In addition to the above stated group holding rules, stopping rules for individual subjects will apply (i.e., indications to withdraw individuals from further vaccinations). These will apply to Cohort A, B and C. The PI will have the responsibility to withdraw from further vaccination individual study participants who present at least one of the following stopping rules for individual subjects:

- Local reactions: upon investigator discretion.

- Systemic solicited adverse events:
  - the subject develops a Grade 3 systemic solicited adverse event beginning within 2 days after vaccination (day of vaccination and one subsequent day) and persisting at Grade 3 for > 2 consecutive days.
- Unsolicited adverse events
  - the subject has any Grade 3 adverse event considered related to vaccination, persisting at Grade 3 for >2 consecutive days.
  - the subject has a serious adverse event considered related to vaccination.
  - the subject has an acute allergic reaction or anaphylactic shock following the administration of vaccine investigational product.
- Laboratory adverse events
  - the subject has any Grade 3 laboratory adverse event considered related to vaccination.
  - the subject, excluding menstruating female, develops hematuria considered related to vaccination.

The PI may, using discretion, ask for the study to be placed on hold and an SMC meeting to be held for any single event or combination of multiple events which, in professional opinion, jeopardize the safety of the subjects or the reliability of the data.

#### **Neurological event monitoring:**

The safety evaluation of study participants will include the use of a standard neurological examination assessing central and peripheral nervous systems, motor and sensory functions upon D0, D6 and D28 post first immunization. New onset of neurological diseases will be reported as AE/SAEs accordingly. The standard neurological evaluation form ([Appendix B](#)) will be used for documentation of the events with objective central or peripheral neurological deficits, in addition to full medically appropriate evaluation according to local procedures.

#### **5.4.4.2. Efficacy futility review**

The planned futility analyses will be conducted by an external statistician who will ensure the maintenance of the blinding of all parties involved in the trial.

Futility analyses will be conducted on efficacy data collected up to 28 days post-challenge (Study Day 105) for the first 46 subjects vaccinated and challenged (Cohort A).

Vaccination of Cohorts B and C will only proceed if the calculated point estimate of increase of vaccine efficacy (VE) in the Ad35.CS.01 – RTS,S/AS01B group over RTS,S/AS01B alone is over 0%, providing a 4 % risk of stopping the trial if the true increase in VE is 50%, assuming an attack rate of 50% in the RTS,S/AS01B group. The probability to stop for futility using these criteria if true increase in vaccine efficacy is 0% is of 40%. The increase in VE of the Ad35.CS.01 group over the RTS,S/AS01B alone

group is defined as  $100 * (1 - \text{AR}_{\text{Ad35.CS.01}} / \text{AR}_{\text{RTS,S}})$  where AR is the attack rate in the 2 groups.

If the above criteria are not met, then vaccination of consecutive cohorts will be performed only if there is agreement between all parties and the study PI.

## 5.5. Outline of study procedures

There will be in total 42 study visits. All study visits during the screening, vaccination challenge and follow-up epochs are applicable for vaccinated volunteers. For infectivity controls, the screening visit 2 during the screening epoch and the study visits during the vaccination epoch are NOT applicable.

The list of study procedures can be found in [Table 7](#) through [Table 10](#) for vaccinees. For infectivity controls, the list of study procedures can be found in [Table 7](#), [Table 9](#) and [Table 10](#).

**Table 7 List of study procedures – Screening epoch (vaccinees and infectivity controls)**

| Epoch                                                                                                       | Screening epoch |                |
|-------------------------------------------------------------------------------------------------------------|-----------------|----------------|
| Study visit                                                                                                 | 1               | 2 † |
| Study day                                                                                                   | -90 to -3       | -7 to -1       |
| Screening, briefing, informed consent                                                                       | ●               |                |
| Comprehension assessment                                                                                    | ○               |                |
| Check inclusion/exclusion criteria                                                                          | ●               | ●              |
| Assign subject number                                                                                | ●               |                |
| Record demographic data                                                                                     | ●               |                |
| Medical history                                                                                             | ●               |                |
| Physical examination                                                                                        | ●               | ○              |
| Check NHANES I criteria and EKG                                                                             | ●               |                |
| Pregnancy test: urine $\beta$ -HCG                                                                          | ●               |                |
| Reporting of SAEs related to study participation or to a concurrent GSK medication/vaccine or any fatal SAE | ●               | ●              |
| Record any concomitant medication/vaccination                                                               | ●               | ●              |
| Urine analysis for safety **                                                                                | ●               |                |
| Blood sampling for safety analysis (7 mL)                                                                   | ● §, v          |                |
| Blood sampling for additional screening analysis (15 mL)                                                    | ● *, v          |                |
| Blood sampling for humoral immunity (20 mL)                                                                 |                 | ● v            |
| Blood sampling for CMI (60 mL)                                                                              |                 | ● v            |
| Blood sampling for exploratory cytokine/chemokine Luminex (2 mL)                                            |                 | ● v            |
| Blood sampling for microarray and deep sequencing analysis (12 mL)                                          |                 | ● v            |
| Blood sampling for plasmablasts FACS and B cell ELISPOT (10 mL)                                             |                 | ● v            |
| Total blood volume in mL per visit                                                                   | 22       | 104     |
| Cumulative blood volume – Immunization groups (mL)                                                          | 22              | 126            |
| Cumulative blood volume – Infectivity controls (mL)                                                         | 22              | -              |

● is used to indicate a study procedure that requires documentation in the individual eCRF

○ is used to indicate a study procedure that does not require documentation in the individual eCRF

†Study visit **NOT** applicable for the infectivity controls

§ Safety labs include hemoglobin, WBC, PLT, ALT, AST, creatinine

\* Additional screening analysis include HIV, HCV, HBV

\*\* **One urine re-sampling is allowed, if necessary, at each time point that a urine sample is taken during the study, at investigators discretion.**

v **One repeat blood draw to refine or confirm whether a potential participant is eligible or not, or to complete an insufficient blood volume is allowed during the screening, when medically justified, at investigators discretion**

(Amended 09 June 2011)

